#### Secondary outcomes

Secondary end points included wound area reduction, 12-month incidence of both recurrence and complete healing, lower limb haemodynamic assessments, incidence of amputation,pain assessment, Wound-QoL assessment, and adverse events.

### Participant timeline

Participants will attend visits at baseline (week-2 and Week 0, randomisation), Week 2, Week 4, Week 6, Week 8, Week 12 and year 1. The CPIPB infusion runs for the first 14 days (Week 0 to Week 2). Data collection points for specific outcomes are outlined in the schedule of assessments (**Table 1**).

**Table 1 T1:** Schedule for data collection, the process of the assessments per visit.

Measures	Baseline	Intervention phase					
Time(weeks)	-2-0	2	4	6	8	12	1 year
Informed consent	√						
Demographics and Past medical history	√						
Physical examination	√	√	√	√	√	√	√
Laboratory Tests	√	√				√	√
Hemodynamic Tests	√	√	√	√	√	√	√
Electrocardiogram	√						
Ascertainment of Inclusion and Exclusion Table	√						
Routine follow-up measurement table	√	√	√	√	√	√	√
Adverse events	√	√	√	√	√	√	√
Endpoint events		√	√	√	√	√	√
Treatment adherence assessment	√	√	√	√	√	√	√

Treatment adherence assessment includes compliance with CPIPB infusion (Weeks 0-2) and long-term standard of care (e.g., offloading, wound care).

#### Baseline data

Demographics, medical history (diabetes type/duration, comorbidities, medications), ulcer characteristics (duration, location, UTC grade, area),electrocardiogram, baseline pain (VAS), baseline haemodynamics (ABI, TcPO2, temperature, PSV), baseline Wound-QoL, laboratory tests.

#### Follow-up data

This includes ulcer healing status, ulcer area measurements, signs of infection, pain scores, hemodynamic measurements, Wound-QoL (assessed at 12 weeks), adverse events, block-related complications, factors related to ulcer recurrence, changes in concomitant medications and treatment adherence.

#### Methods

Clinical examination, validated questionnaires (VAS, Wound-QoL), specific devices for haemodynamic assessment (Doppler, TcPO2 monitor, thermometer), ulcer tracing/photography for area measurement, laboratory analyses, review of medical records. Data will be recorded on standardized Case Report Forms (CRFs), either paper-based or electronic.

### Statistical methods

The primary analysis will be conducted on the intention-to-treat (ITT) population, defined as all randomised participants regardless of adherence or withdrawal.

#### Primary outcome analysis

The proportion of participants achieving complete ulcer healing at 12 weeks will be compared between the CPIPB+SOC group and the SOC group using a chi-square test or Fisher’s exact test, as appropriate. Odds ratios (OR) with 95% confidence intervals (CI) will be calculated using logistic regression, potentially adjusting for important baseline covariates (e.g., baseline ulcer area, UTC grade, duration of the ulcer, and baseline perfusion status (TcPO2)). Furthermore, to explore potential variations in treatment response, prespecified subgroup analyses will be conducted based on baseline ulcer size, UTC grade, and baseline perfusion status.

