#### Sample size

Based on previous research, the healing rate in the SOC group is approximately 47% (21). Our institutional pre-experiment (pilot study) of DFU patients receiving continuous regional block showed that approximately 80% of participants achieved complete wound closure within 12 weeks; thus, we hypothesized that CPIPB + SOC will increase the 12-week healing rate to approximately 80%. To detect this difference with 90% power (β=0.10) at a one-sided significance level of α=0.05, 35 participants are required per group. Accounting for an estimated 10% dropout rate, a total of 78 participants (39 per group) will be recruited.

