#### Secondary outcome analysis

Time-to-event outcomes (time to healing, time to recurrence) will be analysed using Kaplan-Meier curves and compared using the log-rank test. Hazard ratios (HR) with 95% CIs will be estimated using Cox proportional hazards regression, adjusting for covariates.

Continuous outcomes (e.g., percentage area reduction, change in VAS, change in TcPO2, Wound-QoL scores) will be compared using independent t-tests or Mann-Whitney U tests, depending on data distribution. Analysis of covariance (ANCOVA) may be used to adjust for baseline values.

Binary secondary outcomes (e.g., proportion achieving ≥50% area reduction, infection incidence) will be compared using chi-square or Fisher’s exact tests, with ORs and 95% CIs from logistic regression.

Adverse event rates will be summarized descriptively and compared using Fisher’s exact test.

To address missing primary and secondary outcome data, multiple imputation by chained equations (MICE) will be performed as a sensitivity analysis under the missing-at-random (MAR) assumption. No interim analysis is planned for this study due to the relatively modest sample size (n=78). To control the family-wise error rate, the Bonferroni correction will be applied to adjust p-values for multiple comparisons among secondary outcomes. All statistical tests will be two-sided with a significance level set at P < 0.05. Statistical analysis will be performed using SPSS version 18.0 (SPSS, Inc., USA) and GraphPad Prism version 8.2.

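### Adjustment of the reported odds ratio and of the continuous outcomes is left optional, and Bonferroni runs over an unfixed list that includes adverse events: valid, but less efficient and less settled than the baseline data allow

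*Protocol article*

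**What the plan says.** All of this is in the protocol article.

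- **Primary outcome analysis.** Healing proportions are compared by chi-square or Fisher's exact test. The OR comes from logistic regression, "potentially adjusting for important baseline covariates". Ulcer area, UTC grade, ulcer duration and TcPO2 are offered as examples, not as a closed list.
- **Secondary outcome analysis.** Continuous outcomes go to t-tests or Mann-Whitney tests, and "Analysis of covariance (ANCOVA) may be used to adjust for baseline values". Cox regression is described as adjusted, without a qualifier, though its covariates are not named.
- **Multiplicity.** "the Bonferroni correction will be applied to adjust p-values for multiple comparisons among secondary outcomes". The Secondary outcomes section ends its list with "Wound-QoL assessment, and adverse events". Adverse events also get a descriptive summary and a Fisher test in the secondary analysis section.
- **Baseline data.** Ulcer area, duration, UTC grade, TcPO2, PSV, VAS and Wound-QoL are all recorded.
- **Randomisation.** Variable blocks, 1:1, with no stratification factor named.

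**The concern.** With 78 participants and no stratification factor named, chance imbalance in ulcer area, duration or perfusion is likely enough to matter. The data that would deal with it are collected, yet their use is discretionary. Two things follow. First, likely efficiency is given up. Second, the OR and the continuous-outcome estimates can each be reported adjusted or unadjusted, and nothing in the text says which one counts.

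Bonferroni raises a separate question, which baseline data cannot answer. The family includes a harms item, and its size is not fixed. The Abstract lists time to healing, at least 50% area reduction and infection, all absent from the Secondary outcomes section. That section lists amputation, which is absent from the Abstract and from the analysis section.

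**Working it through.** **Plan's own figure.** Inputs from Sample size: "the healing rate in the SOC group is approximately 47"%, "increase the 12-week healing rate to approximately 80"%, "To detect this difference with 90% power", "at a one-sided significance level of α=0.05".

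n = [z_α√(2p̄q̄) + z_β√(p₀q₀ + p₁q₁)]² / (p₁ − p₀)², with p̄ = 0.635.

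- One-sided: (1.645×0.681 + 1.282×0.640)² / 0.33² = 34.5, so 35 per group. 35/0.9 = 38.9, so 39 per group and 78 in all. The figure reproduces.
- Power of the unadjusted test at 39 per group under the two-sided rule in Statistical methods: Φ[(0.33√39 − 1.96×0.681)/0.640] = 87.2%. This is the reference for what follows.

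**Room for covariates.** Expected non-healers: 39×0.53 + 39×0.20 = 28.5. UTC grade with 8 categories takes 7 terms. Area, duration and TcPO2 make 10, and treatment makes 11. 28.5/11 = 2.6 non-healers per parameter. With three covariates plus treatment it is 28.5/4 = 7.1.

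**Primary outcome, power by simulation** (39 per arm, 47% vs 80%, two-sided 5%). Covariate strength is assumed throughout.

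| Method | Assumed strength | Unadjusted | Adjusted |
|---|---|---|---|
| Three covariates, small-sample robust SE | none | 88% | 85% |
| same | modest | 88% | 89% |
| same | strong | 88% | 91–92% |
| Three covariates, linear-model risk difference, robust SE | none | 86.8% | 84.9% |
| same | c ≈ 0.69 | 87.9% | 89.5% |
| same | c ≈ 0.76 | 87.5% | 91.5% |
| same | c ≈ 0.79 | 88.1% | 92.7% |

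Type I error was 4–5% for the first method and 4.4–5.6% for the second. The change in power runs from 85 − 88 = −3 to 92.7 − 88.1 = +4.6 points.

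A likelihood-ratio test with four terms gave 87.2%, 88.1%, 91.7% and 95.1% from no to strong prognostic value, against 87–88% unadjusted. Its type I error was 5.8%, so part of that gain is not real. For the risk difference, the ratio of adjusted to unadjusted variance was 1.07, 1.02, 0.89 and 0.78 with four terms, and 1.15, 1.11, 1.00 and 0.90 with ten. A long list removes most of the benefit. With three covariates and a robust SE that had no small-sample correction, type I error was 6.4–7.9% (5.1–6.4% for the chi-square), so the correction is needed.

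**Odds ratio.** Crude OR: (0.80/0.20)/(0.47/0.53) = 4.5. The conditional OR for the same marginal rates is about 5.5 at c = 0.70, 6.0 at 0.74 and 7.1 at 0.79. Its mean log-scale SE rose from 0.53 to 0.66 (moderate strength, four terms).

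**Continuous outcomes.** With equal variances at baseline and follow-up, Var(ANCOVA)/Var(change score) = (1 − r²)/[2(1 − r)] = (1 + r)/2. This is 0.65, 0.75 and 0.85 at r = 0.3, 0.5 and 0.7. Against the final value alone the ratio is 1 − r²: 0.91, 0.75 and 0.51. The document gives no r.

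**Multiplicity.** The Secondary outcomes section has 8 items if recurrence and 12-month healing count separately. Per-test α: 0.05/8 = 0.00625, or 0.05/7 = 0.00714 without adverse events. At an assumed standardised effect of 0.65, power per test goes from 55.4% to 57.2%. Holm over 8 outcomes that all have that effect averages about 66–68%, against 55% for Bonferroni. For harms, an illustrative event in 6/39 vs 0/39 has Fisher p = 0.025, and 8 × 0.0254 = 0.20 if Bonferroni is applied literally.

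**The case against.** The strongest reply is that nothing here is an error. A chi-square test is valid under randomisation, and Bonferroni controls the error rate it is meant to control. A journal article may leave the final covariate list, the coding of UTC grade and the membership of the multiplicity family to the analysis plan. All of that stands. What remains concerns what the text does fix: an unadjusted test, discretionary adjustment, and a multiplicity rule whose wording takes in harms.

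Four stronger readings are tempting, and the document does not support them.

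- *The primary result can be picked after the fact.* The primary comparison is fixed as chi-square or Fisher, and the final-analysis statisticians stay blinded until the analysis is complete. The open choice concerns the OR and the continuous outcomes. Blinding limits that choice but does not remove it, because coded groups still show which version gives the larger contrast.
- *Adjustment is optional throughout.* Cox regression is stated as adjusted.
- *Adjustment costs nothing.* With non-prognostic covariates it loses 2 to 3 points of power. The eligibility limits on ulcer area, duration and perfusion may also weaken these covariates as predictors.
- *Bonferroni would hide a harm.* Adverse event rates are to be summarised descriptively whatever the p-value, and safety monitoring does not rest on p-values.

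The gap between 87.2% and the planned 90% comes from one-sided sizing with two-sided testing. That is a separate matter, and adjustment should not be presented as its remedy.

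**Conclusion.** The point holds as one of efficiency and pre-specification, not of validity. The clearest gain is ANCOVA: the variance falls to (1 + r)/2 of the change-score analysis, given equal variances and an r that has to be assumed. For the primary outcome a short fixed list changes power by about −3 to +5 points at 39 per arm, with the loss confined to weak or non-prognostic covariates. The sign is therefore likely but not guaranteed. The gain belongs to the risk difference. The conditional OR may be clearly larger than the crude OR and has a larger SE, so it should not be presented as more precise. Taking adverse events out of the family gains only about 2 points per secondary test. The main reason to do so is that an uncorrected p-value is the more useful one for harms. Holm gains more than that and is never less powerful than Bonferroni.

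**What to change.** Before unblinding:

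1. State ANCOVA with the baseline value as the analysis for VAS, TcPO2, PSV and Wound-QoL.
2. Fix one covariate list of at most three or four terms for an adjusted primary analysis, for example log ulcer area, log ulcer duration and TcPO2. Either collapse UTC grade or explain its omission, since it is a named example covariate and a subgroup factor. Report a standardised risk difference with a small-sample-corrected robust SE beside the unadjusted chi-square. If the adjusted OR is also given, label it as conditional.
3. Reconcile the secondary outcome lists into one list of efficacy outcomes, apply Holm to it, and state that adverse events are reported outside that family without correction.

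The cost is a change of wording, a short analysis script (R is already used for the randomisation sequence) and a small loss of power if the chosen covariates turn out not to predict healing.

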#### Secondary outcome analysis

Time-to-event outcomes (time to healing, time to recurrence) will be analysed using Kaplan-Meier curves and compared using the log-rank test. Hazard ratios (HR) with 95% CIs will be estimated using Cox proportional hazards regression, adjusting for covariates.

Continuous outcomes (e.g., percentage area reduction, change in VAS, change in TcPO2, Wound-QoL scores) will be compared using independent t-tests or Mann-Whitney U tests, depending on data distribution. Analysis of covariance (ANCOVA) may be used to adjust for baseline values.

Binary secondary outcomes (e.g., proportion achieving ≥50% area reduction, infection incidence) will be compared using chi-square or Fisher’s exact tests, with ORs and 95% CIs from logistic regression.

Adverse event rates will be summarized descriptively and compared using Fisher’s exact test.

To address missing primary and secondary outcome data, multiple imputation by chained equations (MICE) will be performed as a sensitivity analysis under the missing-at-random (MAR) assumption. No interim analysis is planned for this study due to the relatively modest sample size (n=78). To control the family-wise error rate, the Bonferroni correction will be applied to adjust p-values for multiple comparisons among secondary outcomes. All statistical tests will be two-sided with a significance level set at P < 0.05. Statistical analysis will be performed using SPSS version 18.0 (SPSS, Inc., USA) and GraphPad Prism version 8.2.

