Should this trial demonstrate the superiority of CPIPB plus SOC over SOC alone, the clinical implications would be substantial. This technique could offer a novel, safe, and effective adjunctive therapy for a challenging patient population that currently has limited options. By targeting key pathophysiological drivers of non-healing ulcers, CPIPB could potentially accelerate healing times, reduce the incidence of complications like severe infections, and ultimately lower the rate of major amputations. The findings will also pave the way for future research. Larger, multicentre trials will be necessary to confirm our results and establish the generalizability of the technique. Subsequent studies could explore the optimization of the CPIPB protocol, including the ideal duration of infusion and concentration of local anaesthetic. Furthermore, investigating the efficacy of CPIPB in specific subgroups of DFU patients, such as those with severe ischemic pain who are not candidates for revascularization, would be a valuable next step. In conclusion, this study protocol outlines a trial for a mechanistically targeted therapy that has the potential to significantly improve clinical outcomes and quality of life for patients suffering from the devastating consequences of diabetic foot ulcers.

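### Time to healing: a Kaplan-Meier curve that censors index-site amputation and death would overstate the proportion healed in both arms

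*Protocol article*

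**What the plan says.** Under Secondary outcome analysis the protocol article fixes the methods for time to healing: "Time-to-event outcomes (time to healing, time to recurrence) will be analysed using Kaplan-Meier curves and compared using the log-rank test". It adds: "Hazard ratios (HR) with 95% CIs will be estimated using Cox proportional hazards regression, adjusting for covariates". No cumulative incidence or other competing-event method is named, and no rule says how a patient who is amputated or dies before healing enters this analysis.

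The list under Secondary outcomes includes "12-month incidence of both recurrence and complete healing, lower limb haemodynamic assessments, incidence of amputation". The level and side of the amputations to be counted are not given, and death is not named as an outcome. Under Participant timeline the visits after baseline are at "Week 2, Week 4, Week 6, Week 8, Week 12 and year 1", so follow-up runs well past the 12-week primary endpoint.

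The primary outcome is the proportion healed at 12 weeks, compared by a chi-square or Fisher test. It does not use the time-to-event methods.

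**The concern.** A patient who dies unhealed, or loses the ulcerated part, cannot later meet the definition of complete healing. Kaplan-Meier with that patient censored treats later healing as still possible, at the rate of those who remain under observation. One minus Kaplan-Meier then describes healing in a population where amputation and death do not occur. It no longer estimates the share of randomised patients whose ulcer heals, which is how a healing curve is usually read.

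The published curve would lie above the observed share of patients healed, and would disagree with the 12-week and 12-month healing proportions reported in the same paper. The comparison between arms could also be distorted. The Discussion hopes that the block will "reduce the incidence of complications like severe infections, and ultimately lower the rate of major amputations". If it does, censoring amputations removes more failures from the control curve than from the block curve.

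**Working it through.** **The plan's own figure.** Sample size gives 47% against 80% healed, 90% power, one-sided alpha 0.05. The usual formula for two proportions, with mean proportion 0.635, gives n = [1.645 × √(2 × 0.635 × 0.365) + 1.282 × √(0.47 × 0.53 + 0.80 × 0.20)]² / 0.33² = 34.5, so 35 per arm. Then 35 / 0.90 = 38.9, so 39 per arm and 78 in total. Both stated figures reproduce, and neither depends on this point.

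**Inputs for the check.**
- Healing hazards from the planned rates, taken as constant: SOC l = −ln(0.53)/12 = 0.0529 per week; CPIPB l = −ln(0.20)/12 = 0.1341 per week.
- Competing hazard m (index-site amputation or death). The documents give no rate, so this is an assumption. It is set by q, the 12-week risk of such an event if no ulcer healed: m = −ln(1 − q)/12, equal in both arms, with q = 2%, 5%, 10% and 15%.

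**Formulas.** With competing events censored, one minus Kaplan-Meier estimates 1 − exp(−l·t). The true proportion healed is the cumulative incidence, l/(l + m) × [1 − exp(−(l + m)·t)]. The overstatement is the first minus the second.

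**Example, q = 5%, week 12.** m = 0.00427.
- SOC: 0.0529/0.0572 × (1 − 0.53 × 0.95) = 0.925 × 0.4965 = 45.9%, against 47.0% from Kaplan-Meier: +1.1 points.
- CPIPB: 0.1341/0.1384 × (1 − 0.20 × 0.95) = 0.969 × 0.81 = 78.5%, against 80.0%: +1.5 points.

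**Overstatement in percentage points, equal competing hazards.** The middle column is the competing-event incidence, m/(l + m) × [1 − exp(−(l + m)·12)], times 39.

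| q | Expected competing events by week 12 of 39, SOC / CPIPB | Week 12, SOC / CPIPB | Week 52, SOC / CPIPB |
|---|---|---|---|
| 2% | 0.6 / 0.4 | 0.4 / 0.6 | 2.4 / 1.2 |
| 5% | 1.4 / 1.0 | 1.1 / 1.5 | 5.8 / 3.1 |
| 10% | 2.9 / 2.0 | 2.1 / 3.0 | 11.3 / 6.1 |
| 15% | 4.4 / 3.0 | 3.3 / 4.6 | 16.5 / 9.1 |

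The week-52 column carries the same weekly hazard forward. A q of 2%, 5% or 10% then implies a one-year risk of 1 − (1 − q)^(52/12), about 8%, 20% or 37%, in patients who do not heal. The 15% row implies about 51% and is left out of the summary range. If the one-year risk is instead 5% or 10%, the week-52 overstatement is 1.4 / 0.7 or 2.8 / 1.5 points.

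**Difference between arms.** The Kaplan-Meier difference at week 12 is 33.0 points. The cumulative incidence difference is 32.8, 32.6, 32.1 and 31.6 for the four values of q, so the inflation is about 0.2 to 1.4 points. The standard error of the difference with 39 per arm is √(0.80 × 0.20/39 + 0.47 × 0.53/39) = 10.2 points.

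**When the order of the arms changes.** In the 5% scenario the overstatement becomes larger in SOC from about week 22. At week 12 it becomes larger in SOC if the competing hazard under CPIPB is about 0.7 times that of SOC or less (q = 5%, ratio 0.5: SOC 1.1, CPIPB 0.8). At week 52, q = 5% and equal hazards, the Kaplan-Meier difference is 6.3 points and the cumulative incidence difference 9.0, so the curve would understate the gap.

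**The case against.** Censoring is inferred. The article states no rule, such conventions often sit in a full protocol or analysis plan, and neither is shown. This stands as a limit on the claim. But the article does choose a method, and that method with its default handling does not estimate the proportion healed.

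Log-rank and Cox are not wrong. With competing events censored they validly compare the cause-specific healing hazard. This stands: the fault lies in reading the curve as a probability of healing. Replacing these tests by Gray's test and a subdistribution hazard ratio would change the estimand, and that is a matter of judgement.

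Events may be few. The exclusion criteria remove gangrene, osteomyelitis, exposed bone, severe infection and dialysis, and not every amputation counted need be at the index ulcer. This stands, and it is why the size is given only as a range.

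The 12-month incidence of healing may be analysed as a simple proportion. This also stands: the one-year figures apply only if the healing curve is carried to one year.

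A reader might infer that the overstatement is greatest in the arm that heals more, so that the benefit of the block is inflated. The documents do not support this. Such a result can be obtained by giving both arms the same cumulative competing incidence: at 5% and 10% the difference between arms then grows by 1.7 and about 4 points. With healing incidence h and competing incidence c, however, the implied competing hazard over the 12 weeks is −ln(1 − h − c) × c/(h + c). That is 0.112 against 0.071 at 5% and 0.256 against 0.148 at 10%, a hazard 58% to 73% higher under the block. Nothing in the article suggests that, and the Discussion hopes for the opposite.

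**Conclusion.** The concern holds for the healing curve. If index-site amputation and death are censored, one minus Kaplan-Meier lies above the proportion healed in both arms in every scenario examined: by about 0.4 to 4.6 points at 12 weeks for assumed competing risks of 2% to 15%, and by about 1 to 11 points at one year for 2% to 10%. These figures rest on assumed event rates, on constant hazards equal in both arms, and on the planned healing rates being carried forward unchanged after week 12.

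No direction of bias between arms can be stated in advance. With equal hazards the 12-week effect on the difference is small beside its standard error. The primary outcome, the sample size, and the log-rank and Cox comparisons read as cause-specific are unaffected. This is a minor improvement to a secondary analysis, and it is negligible if such events turn out to be rare.

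**What to change.** Under Secondary outcome analysis, state that time to healing will be presented as cumulative incidence (Aalen-Johansen), with death and amputation at the index ulcer site as competing events. An alternative for the curve is to keep such patients in the risk set as unhealed to the end of the horizon. With no other loss to follow-up the two give the same curve.

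Keep log-rank and Cox on the data with these events censored, and label them as comparing the cause-specific healing hazard. Gray's test or a Fine-Gray model may be added as a supplement. Define which amputations count as index-site.

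The cost is some wording and a competing-risk routine outside the two named analysis packages, for example in R, which the article already uses for the randomisation sequence. Amputation is already a planned outcome; date and site of amputation and date of death need to be on the case report form. The reported healing curve will be slightly lower.

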### Outcomes

#### Primary outcome

The primary study end point was the percentage of ulcers in each group achieving 100% healing at 12 weeks. Complete healing is defined as 100% re-epithelialization without drainage or dressing requirements, confirmed at two consecutive visits 2 weeks apart by an independent, blinded wound specialist. To ensure objective evaluation, wound areas will be traced and verified using computerized planimetry (ImageJ) on standardized digital photographs (taken with fixed distance, positioning, and illumination). These photographs will be securely archived and cross-checked by a central, blinded adjudication committee of two senior plastic surgeons.

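### Time to recurrence is compared between arms by log-rank and Cox, although only healed ulcers can recur and, on the visit schedule, most recurrences are interval-censored over 40 weeks

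*Protocol article*

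**What the plan says.** Under Secondary outcome analysis: "Time-to-event outcomes (time to healing, time to recurrence) will be analysed using Kaplan-Meier curves and compared using the log-rank test". The next sentence adds a model: "Hazard ratios (HR) with 95% CIs will be estimated using Cox proportional hazards regression, adjusting for covariates".

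Under Secondary outcomes the endpoint is a proportion, not a time: "12-month incidence of both recurrence and complete healing".

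Under Participant timeline, with Table 1 in agreement, the visits after randomisation are "Week 2, Week 4, Week 6, Week 8, Week 12 and year 1".

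Under Primary outcome, healing must be "confirmed at two consecutive visits 2 weeks apart by an independent, blinded wound specialist".

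Under Statistical methods, the intention-to-treat population for the primary analysis is "defined as all randomised participants regardless of adherence or withdrawal".

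The article does not state who is at risk of recurrence, when the clock starts, or how the interval after Week 12 is handled.

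**The concern.** Two features of the design do not fit the chosen method.

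- **Risk set.** Recurrence is defined only after healing, which happens after randomisation and is what the treatment is expected to change. If non-healers are left out, each arm is represented by a subset selected by its own treatment. If they are kept as event-free, the arm that heals more has more ulcers that can recur. Neither version compares like with like.
- **Event times.** Kaplan-Meier, log-rank and Cox in their usual form need event dates. Here one interval covers 40 of the 52 weeks of follow-up.

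At stake is the reading of one listed secondary outcome: a hazard ratio for recurrence could depart from 1 in either direction with no effect of the block on recurrence. The primary outcome and the sample size are not affected.

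**Working it through.** **Inputs from the article.** Planning healing rates at 12 weeks are 47% (SOC) and 80% (CPIPB + SOC), with 39 per group (Sample size). Visits are at Weeks 2, 4, 6, 8, 12 and year 1 (Participant timeline).

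**The plan's own figure.** The article gives no figure for recurrence. Its sample size reproduces with the pooled-variance formula, one-sided 0.05, 90% power, mean rate 0.635:

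n = [1.645 × √(2 × 0.635 × 0.365) + 1.282 × √(0.47 × 0.53 + 0.80 × 0.20)]² / 0.33² ≈ 34.6, so 35 per group. Then 35 / 0.90 = 38.9, so 39 per group and 78 in total.

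**Step 1: who can recur.** By Week 12, SOC has 39 × 0.47 = 18.3 healed and CPIPB 39 × 0.80 = 31.2. The difference is 12.9 extra healers. These are 12-week counts; healing between Week 12 and year 1 would add to both and is unknown.

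**Step 2: non-healers dropped.** Assume that 30% of SOC healers recur, that the same 18.33 ulcers would heal and recur at 30% under CPIPB, and that the 12.87 extra healers recur at rate x. CPIPB recurrence is (18.33 × 0.30 + 12.87 × x) / 31.2.

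| x | CPIPB recurrence | SOC recurrence |
|---|---|---|
| 20% | 26% | 30% |
| 30% | 30% | 30% |
| 50% | 38% | 30% |
| 60% | 42% | 30% |

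The sign depends on x, which the article does not give. A simulation in which one latent severity makes ulcers both harder to heal and more likely to recur, with no treatment effect on recurrence, gives an apparent hazard ratio of 1.14 to 1.45 against CPIPB. Its assumptions were 40% one-year recurrence if all healed, a healing log-odds slope of 1 to 2 per SD of severity, and a recurrence log-hazard slope of 0.5 to 1.

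**Step 3: non-healers kept as never at risk.** Even if every healed ulcer has the same 30% recurrence, recurrence among all randomised is 18.33 × 0.30 / 39 = 14% in SOC and 31.2 × 0.30 / 39 = 24% in CPIPB. The excess arises only because more ulcers healed.

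**Step 4: the visit gap.** 52 − 12 = 40 weeks, and 40 / 52 = 77% of follow-up. Assume a constant hazard with one-year recurrence r, so λ = −ln(1 − r) / 52. For an ulcer healed at Week h, the share of its recurrences by year 1 that fall after Week 12 is [exp(−λ(12 − h)) − exp(−λ(52 − h))] / [1 − exp(−λ(52 − h))]. For r of 30% to 40% this is 80% to 81% at h = 4, 89% to 90% at h = 8, and 100% at h = 12.

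**Step 5: effect of dating events at the visit.** A recurrence found at year 1 is recorded at 52 − 4 = 48 weeks from healing if the ulcer healed at Week 4, and at 52 − 12 = 40 weeks if it healed at Week 12. Later healers therefore seem to recur sooner. This was simulated with the same recurrence hazard in both arms (30% to 40% at one year), healing at Weeks 4, 6, 8 or 12, and one arm healing earlier:

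- True dates, clock from healing: hazard ratio 1.0.
- Visit dates, clock from healing: about 0.5 to 0.6, in favour of the earlier-healing arm, when healing times clearly differ. For example, healing split 40/30/20/10% against 10/20/30/40% over the four visits gives about 0.6. A milder split of 30/30/20/20% against 15/20/30/35% gives 0.75 to 0.78.
- Visit dates, clock from randomisation: about 1.06, slightly against the earlier-healing arm.

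**Step 6: the alternative.** Counting only healing by Week 12, the proportion healed and not recurred at year 1 is 18.33 × 0.70 / 39 = 33% in SOC. In CPIPB it is (18.33 × 0.70 + 12.87 × (1 − x)) / 39, which runs from 59% (x = 20%) to 46% (x = 60%). Every randomised participant is in the denominator.

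**The case against.** The strongest reply is that risk set, time origin and censoring rules are details that an article commonly leaves to the full protocol or analysis plan, and that the article nowhere says non-healers will be dropped. That is fair, and their absence is not the point. The article does fix the method, the schedule and a 12-month incidence endpoint, and these do not fit together. Steps 2 and 3 show that neither treatment of non-healers restores a randomised comparison. Better dating would not restore it either.

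A second reply is that recurrence dates may be available. Recurrences up to Week 12 are bracketed within 2 to 4 weeks, and the article lists medical record review as a data source and regular follow-up within SOC. This stands in part: a reader might infer that recurrence times are wholly unobserved, but the text supports only that most are interval-censored over 40 weeks unless dated elsewhere. The article does not tie either source to dating recurrence.

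Two stronger readings should be resisted. A reader might infer that the analysis is biased against CPIPB. That requires harder-to-heal ulcers to recur more often, which the document does not say; at equal recurrence rates the healed-only comparison shows no bias. A reader might also infer that earlier healers are penalised by longer time at risk before year 1. With true dates and the clock from healing, censoring handles this. With visit dates and that clock the distortion favours the faster arm, and it runs slightly the other way only with the clock from randomisation.

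**Conclusion.** The point holds. As written, the log-rank and Cox comparison of time to recurrence is a comparison of groups selected after randomisation, with most event times interval-censored over 40 weeks. At the planning rates the sets that can recur by Week 12 are about 31 and 18 of 39.

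The loss of randomised comparability needs no assumption beyond treatment affecting healing. The size and sign of the resulting bias do need assumptions: with 30% recurrence in SOC healers and 20% to 60% in the extra CPIPB healers, CPIPB recurrence is 26% to 42%. The distortion from visit dating (hazard ratio about 0.5 to 0.6, or about 1.06, according to the clock) assumes equal constant hazards and clearly different healing times, and shrinks as healing times converge.

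The consequence is limited to one secondary outcome among several that are Bonferroni-adjusted. The article's hypothesis concerns healing and safety, not lower recurrence, so nothing here weakens the primary comparison.

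**What to change.** - Make the between-arm comparison a binary outcome in all 78 randomised participants: index ulcer healed and not recurred at year 1, with a risk difference and 95% CI. This agrees with the 12-month incidence already listed and with the intention-to-treat population.
- Count amputation or death before year 1 as not ulcer-free. Count a missing year 1 assessment as not ulcer-free, with the planned multiple imputation as the sensitivity analysis.
- State how healing first seen at year 1 meets the two-visit confirmation rule, since no scheduled visit follows it.
- Report recurrence among healed ulcers descriptively by arm, without a log-rank test or hazard ratio.

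**Cost.** One secondary endpoint is redefined. No added visit or larger sample is needed, because endpoint events are already collected at year 1. The main weakness is that an ulcer that recurs and heals again between Week 12 and year 1 may be misclassified, so participants should be asked about this at the year 1 visit.
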